| The sample size was determined by using change in body fluid as the primary outcome measure and by extrapolating expected changes and standard deviation from data in the study of the effect of pioglitazone in T2DM patients. The target sample size was 37 subjects per group that will provide 80% power to detect a significant effect, using a 2-sided, *p*=0.05. **Formula:**  **Value description**  ** = 0.05 (two-tail)  = 1.96**  ** = 0.20  = 0.84**  **[figure not shown]**  **n = **  **[figure not shown]**  By the calculation, the quantity of subject per group is 37. But with the follow up, the 10% loss follow up of the calculated number is considered. Therefore, the quantity of subject per group is 40, total is 80.  Statistical analyses were performed using the Statistical Package for Social Sciences (SPSS) software version 11.5. Intention-to-treat analysis was used by replacing the missing data with series mean for each group. Both descriptive and inferential statistics were determined. A bi-directional α-level of significance was set at *p*= 0.05 for all measures.   - Descriptive statisticsa was used for demographic results which are expressed as mean (± standard deviation; SD) and percentage unless otherwise indicated. - Chi-square tests were used for evaluating categorical variables. - Continuous variables between study and control groups were compared with unpaired *t-*tests. - Continuous variables between baseline and at the end of study for each group of patients were compared by using paired student *t-* tests. - Analysis of covariance (ANCOVA) was used for controlling covariate factors if baseline data are different between the patient groups. - One-way repeated analysis of variance (ANOVA) was used to examine the main effects of time when comparing data obtained at one time to data obtained at another time during the study period. - One-way repeated analysis of variance (ANOVA) with between-subjects factor was used to determine the main effects of overall difference between the control and the study groups with respect to the mean of the data. |
|  |
| ***13. Details of any clinical safety reporting processes and when applicable, specific risk management interventions to safeguard subjects*** |

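### Section 12 lists several between-arm tests at two-sided 0.05 and names none as deciding for change in body fluid, so the false-positive rate could be about 0.08 to 0.10

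*Protocol*

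**What the plan says.** Section 12 of the protocol covers both sample size and analysis. On sample size it states: "The sample size was determined by using change in body fluid as the primary outcome measure". It adds: "The target sample size was 37 subjects per group that will provide 80% power to detect a significant effect".

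The analysis list that follows refers to continuous variables in general:

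- **Unpaired t-test between arms:** "Continuous variables between study and control groups were compared with unpaired" t-tests.
- **Paired t-test within each arm:** "Continuous variables between baseline and at the end of study for each group of patients were compared by using paired student" t-tests.
- **ANCOVA:** used to control covariates if the arms differ at baseline. The section gives no criterion for a difference and no list of covariates.
- **Repeated-measures ANOVA for time.**
- **Repeated-measures ANOVA with a between-subjects factor,** which "was used to determine the main effects of overall difference between the control and the study groups with respect to the mean of the data".

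One significance rule covers everything: "A bi-directional α-level of significance was set at" 0.05 for all measures. No test is called primary or tied to change in body fluid, and no order or multiplicity rule is given.

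**The concern.** Both objectives in Section 3 compare 7.5 mg with 15 mg, so a between-arm contrast has to decide the trial. Change in body fluid is continuous, so three listed between-arm tests apply to it, and they answer different questions. The unpaired t-test on change and the ANCOVA look at the end of study. The repeated-measures group effect averages over visits, and if baseline is one of the time points it dilutes any treatment effect. The tests can therefore disagree on the same data. If the choice is made after the data are seen, the stated 0.05 no longer describes the chance of a false claim. This matters more in an open-label trial in which, under Section 4, the investigator randomizes and dispenses.

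The ANCOVA raises a further difficulty. Whether it is used depends on an observed baseline difference that the plan does not define, so two analysts could follow the text and report different results.

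The within-arm paired tests are a secondary matter. Both arms receive active drug, and Section 2 names fluid retention as a common side effect of the class. A shared gain is therefore plausible, and one arm can easily reach p<0.05 while the other does not.

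**Working it through.** **1. The plan's own figure.** Section 12 gives 37 per group for 80% power at two-sided 0.05, with z-values 1.96 and 0.84. The expected change and SD are in figures that are not shown, so 37 cannot be recomputed forward; that is no fault of the plan. Solving backwards for a two-arm comparison of means:

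delta/SD = (1.96 + 0.84) × √(2/37) = 2.80 × 0.2325 = 0.651

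The normal-approximation power at that value with 37 per arm is 0.800. The figure is therefore consistent with a between-arm comparison of two means, but the visible text does not link it to one of the listed tests.

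**2. Inputs for the error rate.**

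- From the protocol: 37 per arm, equal allocation, two-sided 0.05, and visits at baseline and weeks 4, 8, 12, 16, 20 and 24.
- Assumed: body fluid measured at all seven time points (Section 11 describes bioimpedance without a schedule); compound symmetry with correlation 0.3 to 0.9; ANCOVA triggered by a baseline t-test with p<0.05; no true dose difference.

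**3. Simulated false-positive rates** (12,000 to 20,000 trials per setting).

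| Rule for declaring a dose difference | Rate |
| --- | --- |
| Any single between-arm test, fixed in advance | 0.047 to 0.053 |
| t-test on change, or conditional ANCOVA | 0.047 to 0.053 |
| Those two, or repeated-measures group effect on change scores | 0.077 to 0.083 |
| Those two, or repeated-measures group effect on raw values | 0.092 to 0.101 |
| t-test on change, t-test on end values, unconditional ANCOVA, or repeated-measures effect | about 0.11 to 0.13 |

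The inflation comes from the choice between the end-of-study comparison and the repeated-measures effect. Adding the conditional ANCOVA to the t-test alone leaves the rate essentially unchanged. For scale, three independent tests would give 1 − 0.95³ = 0.143; the real tests are correlated, so the rate is lower.

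**4. Within-arm paired tests.** Let p be the power of the paired t-test in one arm (noncentral t, n = 37) when both arms share the same true gain. Just one arm is significant with probability 2p(1 − p); only the 15 mg arm with probability p(1 − p).

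| Assumed shared gain (SD of change) | p | One arm only | 15 mg arm only |
| --- | --- | --- | --- |
| 0.2 | 0.219 | 2 × 0.219 × 0.781 = 0.34 | 0.17 |
| 0.33 | 0.497 | 2 × 0.497 × 0.503 = 0.50 | 0.25 |
| 0.4 | 0.658 | 2 × 0.658 × 0.342 = 0.45 | 0.23 |
| 0.5 | 0.841 | 2 × 0.841 × 0.159 = 0.27 | 0.13 |

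With no change in either arm, the one-arm-only rate is 2 × 0.05 × 0.95 = 0.095.

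**The case against.** **The protocol never says that any significant test will decide.** True. The problem is what the silence permits, and the rates above are conditional on that use.

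**A separate SAP could name the deciding test.** It could, and none is shown. But Section 12 presents itself as the analysis plan. It gives several tests equal standing and makes one depend on the observed data without a criterion. This weakens the point without removing it.

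**The paired tests are ordinary within-group summaries.** This stands. A reader might infer that the plan treats a significant rise on 15 mg with none on 7.5 mg as proof of a dose difference. The text does not support that: it describes the paired tests only as baseline versus end of study in each arm. The 0.27 to 0.50 figures describe a misuse that the plan does not prescribe, and in the direction the trial hopes for they are halved.

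**The error is not more than doubled.** A reader might infer that it is. That needs a t-test on end values, which is not the stated change outcome, and an ANCOVA available unconditionally. With the tests as listed, the rate is about 0.08 to 0.10.

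**The contrast behind the sample size may be in the missing formula.** This also stands. The phrase "will provide 80% power to detect a significant effect" does not itself name a contrast, but the per-group figure and the objectives point between arms. An undefined sample-size contrast is not charged to the plan here.

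**Conclusion.** The point holds in a limited form. Section 12 names a primary outcome without naming the between-arm test that decides it. Free choice among the listed tests gives a false-positive rate of about 0.08 to 0.10 against the stated 0.05, and about 0.11 to 0.13 only under the wider set of routes. These figures rest on the assumed seven-point body-fluid schedule, compound symmetry and baseline p<0.05 trigger. The wording around the paired tests is a lesser matter: they need a label, because comparing the two arms' p-values would mislead, but the plan does not propose to do so. The point should be corrected before analysis; it does not call the design into question.

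**What to change.** In Section 12, state that the trial is decided by one analysis: the 7.5 mg versus 15 mg difference in change in body fluid at week 24, from an ANCOVA with baseline body fluid as a covariate set in advance, two-sided 0.05, reported with its 95% confidence interval. Name the single body-fluid measure, since Section 11 lists intracellular, extracellular and total body water and the contrast is not unique until one is chosen. Remove the trigger based on observed baseline imbalance. Label the unpaired t-test and the repeated-measures group effect supportive. Label the within-arm paired comparisons descriptive and not evidence of a dose difference.

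This takes a few sentences. It needs no extra patients or visits and no additional baseline measurement, because the change score already requires one. The price is that the alternative tests can no longer carry the primary claim.

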| **Expected number of subjects: 74 subjects**  **Inclusion criteria**   1. Age 18 years or older 2. Diagnosed T2DM with stable glycemic treatment with HbA1c>8% at least 12 weeks and diagnosed CKD according to [Kidney Disease: Improving Global Outcomes](https://www.google.co.th/url?sa=t&rct=j&q=&esrc=s&source=web&cd=8&cad=rja&uact=8&ved=0ahUKEwid7tCq8rPLAhVDBY4KHaXbAs8QFggyMAc&url=https%3A%2F%2Fwww.guideline.gov%2Fbrowse%2Fby-organization.aspx%3Forgid%3D2349&usg=AFQjCNFB0TRXT4TlgKTcrEguhdpN6NSZxg) (KDIGO) 2012 definition 3. No history of treatment with TZDs within 12 weeks before starting the study 4. Normal liver function, which referred to AST less than 105 U/L and ALT less than 120 U/L 5. Subject with signed consent form.   **Exclusion criteria**   1. Active malignancy 2. Severe heart, lung or liver disease, stroke, chronic infection, e.g., tuberculosis within one year of starting the study 3. Limited life expectancy within 12 months, edematous state from any cause 4. Specific contra-indications to pioglitazone including increased serum levels of liver enzyme (aspartate aminotransferase [AST] or alanine aminotransferase [ALT] >2.5 times the upper limit of normal), and history of bladder malignancy. 5. Subject without signed consent form   **Withdrawal or termination criteria**   1. The occurrence of heart failure or volume overload after drug administration which resulted in treatment needed or consent form withdrawal. 2. The occurrence of side effect which resulted in consent form withdrawal such as dizziness that affect driving, diarrhea that affect routine life. 3. The occurrence of severe infection, cardiac arrhythmia, myocardial infarction and cardiovascular hospitalization.   **Subject allocation**  Block randomization divides subjects into low dose group and standard dose group equally. A randomization in each group is conducted by dividing each subgroup into 20 groups with the setting number 0-19. The even number group, classified as A, is the intervention group. And the odd number group, classified as B, is the control group. |
|  |
| ***11. Key study assessments and procedures*** |

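### Baseline adjustment is made to depend on an observed baseline difference; one ANCOVA fitted regardless of balance would cost nothing and gain about 1 to 12 points of power on the primary outcome

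*Protocol*

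**What the plan says.** All of the relevant analysis text is in Section 12 of the protocol.

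- Default test between arms: "Continuous variables between study and control groups were compared with unpaired" t-tests. The text does not say whether the variable is the end-of-study value or the change from baseline.
- Adjustment: "Analysis of covariance (ANCOVA) was used for controlling covariate factors if baseline data are different between the patient groups". No criterion for a difference is given and no covariates are named.
- A repeated-measures ANOVA with a between-subjects factor is also listed for the overall group difference, with no baseline covariate stated.
- Primary outcome: "The sample size was determined by using change in body fluid as the primary outcome measure". No analysis bullet ties this outcome to a particular test.
- Size: "The target sample size was 37 subjects per group that will provide 80% power to detect a significant effect", with "A bi-directional α-level of significance was set at *p*= 0.05 for all measures". The expected change and its SD are in figures that cannot be read here.

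Section 10, under subject allocation, makes the arms equal in size by block randomisation.

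**The concern.** After randomisation any baseline difference between the arms has arisen by chance. Whether it happens to look large says nothing about how well baseline predicts outcome, and that is what decides whether adjustment helps. If the trigger is a 5% test, it fires in about 5% of trials per variable, so the unadjusted t-test decides nearly every trial and the precision available from baseline is mostly left unused.

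The rule also makes the choice of between-arm test depend on the data. At stake are some power in a trial planned at 80%, a test that does not sit exactly at its nominal level, and a primary comparison that is not fixed to one model.

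**Working it through.** **Inputs.** From Section 12: two-sided alpha 0.05 (1.96), power 80% (0.84), 37 per arm. From Section 10: 1:1 allocation. Assumed, because the document does not give them in readable form:

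- the standardised effect on change, d;
- the correlation rho between baseline and week 24, taken as 0.3 to 0.9, with equal SDs at both times;
- the trigger, taken as p<0.05 in a t-test on the outcome's own baseline.

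**Step 1: the plan's own figure.** The sample size cannot be computed forward without the effect and SD. Back-solving n = 2(1.96 + 0.84)²/d² with n = 37 gives d = sqrt(2 × 7.84/37) = 0.651. Power at 37 per arm is then 0.80. This is circular and serves only as a consistency check.

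**Step 2: what ANCOVA gains over a t-test on change.** With SD the common SD of body fluid:

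- variance of change = 2(1 − rho) × SD²
- residual variance after ANCOVA = (1 − rho²) × SD²
- ratio = (1 + rho)/2, that is 0.65, 0.75, 0.85 and 0.95 at rho 0.3, 0.5, 0.7 and 0.9.

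Equivalently, ANCOVA would match the precision of 37 per arm on change with 37 × (1 + rho)/2 = 24.05, 27.75, 31.45 and 35.15, rounded up to 25, 28, 32 and 36 per arm.

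**Step 3: the conditional rule on the primary outcome.** Simulated trials with 37 per arm and d = 0.651 on change; ANCOVA if the baseline t-test has p<0.05, otherwise a t-test on change.

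| rho | Power, conditional rule | Power, ANCOVA always | Difference (points) | Type I error, conditional rule |
|---|---|---|---|---|
| 0.3 | 80.3% | 92.6% | 12.3 | 4.0% |
| 0.5 | 80.1% | 88.8% | 8.7 | 4.3% |
| 0.7 | 79.7% | 84.8% | 5.1 | 4.7% |
| 0.9 | 79.1% | 80.4% | 1.3 | 4.9% |

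Repeat simulations agreed to within one point. The lowest type I error across them was 3.9%, and ANCOVA always stayed at 5.0%.

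**Step 4: why the rule errs on the low side.** At rho 0.3 under the null, the trigger fires in 5.02% of trials, where ANCOVA rejects 4.91%. In the other 94.98% the t-test rejects 3.99%. Together, 0.0502 × 0.0491 + 0.9498 × 0.0399 = 0.040. The rule switches to ANCOVA in just those trials where the t-test would have rejected too often (23.7%), and what remains is below 5%.

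**Step 5: the end-value reading.** The wording would also permit a t-test on week 24 values. Holding the effect at 0.651 SDs of change, the effect in SDs of the end value is 0.651 × sqrt(2(1 − rho)): 0.504 at rho 0.7 and 0.291 at rho 0.9.

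| | rho 0.7 | rho 0.9 |
|---|---|---|
| Power, t-test on end values | 57% | 24% |
| Power, conditional rule on end values | about 59% | about 25% |
| Power, ANCOVA always | 85% | 80% |
| Type I error, conditional rule | 3.6% | 2.3% |

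**The case against.** The strongest reply is that the named primary outcome is a change score. Change already uses baseline by subtraction, and an unpaired t-test on change in a randomised trial is valid, unbiased and consistent with how the trial was sized. Under that reading the trial keeps essentially its planned 80%, and if body fluid correlates with its own baseline at about 0.9 the loss is only about one point. This stands, and it sets the weight of the point.

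Three stronger readings might be inferred, and the document does not support them.

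- **That the primary analysis has only 25% to 59% power.** This needs end values to be tested. Section 12 leaves that open for continuous variables in general, but names change for the primary outcome.
- **That the rule inflates the false-positive rate.** Followed mechanically, it was conservative in every case computed. Inflation to 6.1% to 7.7% on change scores (6.4% to 9.3% on end values) would require reporting whichever of the t-test and ANCOVA is significant. The undefined trigger does not exclude this, but nothing says it is intended.
- **That baseline information is thrown away altogether.** This is wrong for a change score.

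It is also fair to say that the trigger used in the calculation is a construction. Section 12 states no test or threshold, and its covariates could be variables other than the outcome's own baseline.

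The repeated-measures ANOVA does not answer the point. It has no stated baseline covariate, and it adds a further between-arm analysis without saying which is primary.

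**Conclusion.** The point holds as a matter of efficiency and prespecification. On change in body fluid, the conditional rule gives up about 12, 9, 5 and 1 points of power against ANCOVA always at correlations 0.3, 0.5, 0.7 and 0.9, with type I error of 3.9% to 4.9% instead of 5%. Larger losses apply only to variables compared as end-of-study values.

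The figures rest on a back-solved effect of 0.651, 37 evaluable subjects per arm, an assumed correlation and an assumed p<0.05 trigger. The direction does not depend on them: across the range examined, ANCOVA fitted regardless of balance was at least as powerful and held its level. Because the t-test on change is valid and keeps close to the planned power, this is a free improvement and not something that must be fixed before the trial can be interpreted.

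**What to change.** In Section 12, replace the t-test and conditional ANCOVA bullets with one statement along these lines:

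*The primary between-arm comparison is the difference in body fluid at week 24, estimated by ANCOVA with treatment group and the baseline value of body fluid as covariate, fitted regardless of observed baseline balance. The same model, each with its own baseline value, is used for weight, extracellular water, HbA1c and fasting glucose. The unadjusted t-test and the repeated-measures ANOVA are supportive.*

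Delete the baseline-difference trigger. Name this one model only, so that the choice of primary analysis is not reopened. With baseline as covariate, modelling the week 24 value or the change gives the same treatment estimate, so the primary outcome used for sizing is unchanged.

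The cost is wording alone. A change in body fluid or weight already needs a baseline value, and Section 4 schedules HbA1c and fasting glucose before the first treatment. The sample size can stay as it is.
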